**Figure 1 F1:**
[figure not shown]
MODERNISED study workflow. CRF, clinical research facility; SCTU, Southampton Clinical Trials Unit; UHS, University Hospital Southampton.

### Baseline data collection

Clinic and MDT lists will be screened regularly (minimum two times per day) to identify cancer cases referred to relevant clinics. Clinic and 28-day faster diagnosis pathway lists will also be used to identify individuals referred to secondary care by their general practitioner for symptoms, which indicate that they may have one of the 10 cancers being investigated. Healthy volunteers are recruited from registers where they have consented to be approached for involvement in research and will be contacted by the research team. If recruitment of healthy volunteers is challenging, the protocol allows for members of staff at the University Hospital Southampton and the University of Southampton to be approached. Those providing informed consent will be invited to a baseline visit (T_0_).

At the baseline visit, eligibility will be confirmed with a trained and delegated healthcare professional, who will also collect medical history, concomitant medications, demographics and the Index of Multiple Deprivation. Pseudonymised data will then be entered into Medidata’s Rave Electronic Data Capture, which can then only be accessed by allocated staff at SCTU. Participants will then have 4 mL of blood drawn into an EDTA tube. Any adverse events related to blood collection will be reported to the SCTU and summarised in the final study publication. All blood samples will be posted overnight Monday to Thursday at ambient temperature using Royal Mail Safeboxes (or equivalent) to the University Hospital Southampton NHS Foundation Trust, Wessex Investigational Sciences Hub (WISH). The Enlighten assay will be performed by Southampton ECMC-trained laboratory personnel housed in the WISH laboratory, and pseudonymised assay results (participant identifier and amino acid readings) will be transferred securely to PD to be converted to amino acid concentrations.

### Outcome measurement

Cancer outcome and staging will be retrieved from the Electronic Health Record (EHR) via local hospital research staff. This will be triggered for each participant once 3 months have passed since informed consent (T_1_), but data may be entered earlier where appropriate. Cancer diagnosis will be coded using ICD-10 to capture ToO, morphology and staging according to TNM (tumour, node, metastases) and cancer-specific staging system, as appropriate. Consent will be gained to collect further cancer diagnoses up to 2 years from participants’ enrolment.

### Model training and validation

Participants will be randomised in a 3:1 ratio with varying permuted blocks, balanced by cancer ToO and stage, into a model training (75% of participants) or model validation (25% of participants) set. The randomisation list will be pregenerated by a statistician at SCTU. Those in the model training set will have their cohort (cancer case, symptomatic control and asymptomatic control), age and sex shared with PD to train machine learning algorithms in combination with amino acid concentrations. PD will be blinded to the diagnostic status of participants in the model validation set.

Symptomatic controls and healthy volunteers may later be diagnosed with cancer (and therefore move into the cancer cases cohort). Randomisation will therefore only occur on three occasions during the study to reduce the impact of imbalance between building and validation sets. All participants and care providers will remain blinded. Participants will not be randomised more than once. The occasions are as follows: (1) when the amino acid concentrations have been measured for the first batch of 20 participants’ samples with complete data (to stress test processes). (2) When the T_1_ visit has occurred for 50% of the target participants in the breast, colorectal, prostate and lung cancer cohorts. (3) When the T_1_ visit has occurred for all participants, and all data have been returned.

### Machine learning training and validation

Machine learning techniques considered will include: random forests, support vector machines, ensemble subspace discriminant classifiers, XGBoost, neural networks and deep learning algorithms. The final modelling strategy will be informed by comparative predictive performance and computational cost. Triplicate values of the five amino acids (Cysteine, Reduced Cysteine, Lysine, Tryptophan and Tyrosine) will be used as input parameters (or combined as average readings), with potential additions of participant age and sex. Feature importance will be measured by Shapley values. Stratified cross-validation will be used to reduce overfitting.

One algorithm will predict diagnostic status (‘cancer’ or ‘no cancer’), a second will predict cancer ToO (bladder, breast, colorectal, lung, melanoma, oesophageal, ovarian, pancreatic, prostate and renal) and a third will predict cancer stage (I, II, III, IV). The trained algorithms will use amino acid concentrations (and potentially age and sex) to predict diagnostic status, ToO and cancer stage in the development and validation cohorts. These predictions will be provided to statisticians at SCTU to independently validate predictions against true status.

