### The Proteotype Diagnostics Enlighten test

Proteotype Diagnostics (PD) have developed an alternative approach to MCED testing. Instead of measuring material released from tumours (cfDNA or ctDNA), amino acid concentrations are measured in plasma in the Enlighten test, which are affected by the immune response. Immune responses are stronger during the early stages of cancer^12^ and therefore may be used to improve the detection of stage I and II cancers. Machine learning (an ensemble subspace discriminant classifier) was applied to classify tested samples to cancer or non-cancer in a retrospective observational study of 77 cancer patients (breast, colorectal, pancreatic and prostate) and 20 healthy volunteers. A sensitivity of 78% at 100% specificity was achieved using Enlighten, and concentrations were further differentiated in early-stage cases.^13^

Southampton Experimental Cancer Medicine Centre (ECMC) responded to an open call for partnerships with PD to develop a study further evaluating the Enlighten test. Southampton Clinical Trials Unit (SCTU) then developed a research proposal with PD and ECMC as partners, which is academically sponsored by University Hospital Southampton Trust and jointly funded by the National Institute for Health and Care Research and the Office for Life Sciences (ref NIHR207538).

The primary aim of this study is to train a machine learning classifier to use amino acid concentrations from the Enlighten test to detect cancer (bladder, breast, colorectal, lung, melanoma, oesophageal, ovarian, pancreatic, prostate and renal) in comparison to adult participants with symptoms of cancer where a cancer diagnosis was ruled out and healthy volunteers. Participants will be randomised, with 75% used to train the classifier and 25% used to validate the classifier. Secondary aims include:

Training and validating a classifier to distinguish cancer patients from adult participants with symptoms of cancer, where a cancer diagnosis was ruled out.Training and validating a classifier to distinguish cancer patients from healthy controls.Evaluating discrimination and sensitivity by tissue of origin (ToO), stage, age, sex at birth and availability of a UK cancer screening programme.Training and validating a classifier to predict ToO.Training and validating a classifier to predict cancer stage.

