## Methods and analysis

### Study design

MODERNISED (ISRCTN17299125) is a multicentre prospective, non-interventional, case–control study recruiting 1000 participants with known cancer, 250 under investigation for cancer where cancer was ruled out, and 100 healthy volunteers. Participants will be recruited from five secondary care sites and healthy volunteer register banks, or hospital or university staff in England. Recruitment began in January 2025. Recruitment is underway, and version 2 (01 April 2025) is the latest version of the study protocol at the time of submitting this manuscript. Important protocol modifications are reported to relevant parties as part of the SCTU’s standard operating procedures.

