### Study participants

The first cohort, ‘cancer cases’, will consist of 1000 adults recently diagnosed with one of the 10 cancers, recruited from secondary care sites prior to treatment. The second cohort, ‘symptomatic controls’, will consist of 250 adults either currently or previously under investigation for one of the 10 cancers, recruited from secondary care sites, who are found to be cancer-free following normal diagnostic pathways. Participants in this cohort who are found to have cancer during follow-up will be moved to the cancer cases cohort. These participants will be reached via screening of clinic lists and approached during routine hospital visits for symptom investigation, or by phone call to invite them to attend an enrolment visit. The third cohort, ‘healthy volunteers’, will consist of 100 adults with no known cancer and no active symptoms indicative of cancer, recruited from volunteer groups at secondary care sites, or University and hospital staff if recruitment is slower than anticipated. These participants will be reached by advertisement of the study in email newsletters and invited to attend recruitment clinics. Participants in this cohort who are found to have cancer during follow-up will be moved to the cancer cases cohort. Full inclusion and exclusion criteria can be found in table 1. The study workflow is outlined in figure 1.

**Table 1 T1:** Inclusion and exclusion criteria

Entry arm	Inclusion criteria	Exclusion criteria
All	1. Age 18 years or older. 2. Able to provide a written informed consent. 3. Willing to provide a 4 mL blood sample at the time of enrolment.	6. Pregnancy (by self-report of pregnancy status), or pregnancy within the last 12 months. 7. Current febrile illness. 8. Infection requiring hospitalisation within 30 days prior to blood draw. 9. Acute exacerbation or flare of an inflammatory condition requiring escalation in medical therapy within 14 days prior to blood draw. 10. Undergone a surgical procedure (including diagnostic biopsy) within 14 days prior to blood draw. 11. Undergone a blood transfusion within 30 days prior to blood draw. 12. Recipient of organ transplant or prior allogeneic stem cell transplant. 13. Poor health status or unfit to tolerate a blood draw. 14. Oral or intravenous corticosteroid use in the past 14 days prior to blood draw.

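### Age and sex may enter the classifier in a case-control sample with no described matching, and no stated analysis isolates what the amino acids add, so the primary AUROC could be inflated

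*Protocol article*

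**What the plan says.** The protocol article states the primary aim as to "train a machine learning classifier to use amino acid concentrations from the Enlighten test to detect cancer" (The Proteotype Diagnostics Enlighten test). The measure is the AUROC for cancer against no cancer, with both control groups pooled.

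The section Machine learning training and validation lists five amino acids as inputs, "with potential additions of participant age and sex". It adds: "The final modelling strategy will be informed by comparative predictive performance and computational cost". Under Model training and validation, the test developer receives training-set participants' cohort, with "age and sex shared with PD to train machine learning algorithms in combination with amino acid concentrations".

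Study design describes a "multicentre prospective, non-interventional, case–control study recruiting 1000 participants with known cancer". The only age criterion in the eligibility table is "Age 18 years or older", and no age or sex matching is described. The 250 symptomatic controls are "recruited from secondary care sites, who are found to be cancer-free following normal diagnostic pathways". The 100 healthy volunteers are "recruited from volunteer groups at secondary care sites, or University and hospital staff if recruitment is slower than anticipated".

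The 3:1 training/validation split is random within the recruited sample and balanced on tissue of origin and stage only. The Analysis plan summarises demographics by cohort and repeats the analyses by control type, age band and sex. Separate classifiers against each control type are secondary aims, and Shapley values will measure feature importance.

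**The concern.** The article does not settle whether the primary AUROC belongs to the amino acids alone or to the amino acids together with age and sex, and it makes predictive performance a criterion for the choice. In a case-control study the age and sex make-up of each cohort depends on how it was recruited. If the cohorts differ, a model given age and sex can use that difference, and the gain would be counted towards the Enlighten test.

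The held-out 25% cannot reveal this, because it is drawn from the same cohorts and carries the same difference. A score built only on amino acids does not fully settle the matter either: amino acid levels may themselves track age. That is a possibility the article does not address, not something it shows.

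At stake is the interpretation of the headline result. The Discussion foresees triage of people with suspected cancer before imaging. Age and sex are already known there, so the useful quantity is what the assay adds to them, and no stated analysis reports it.

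**Working it through.** **1. The plan's own benchmark.** The Sample size calculation says that 337 validation participants (250 cases, 62 + 25 = 87 controls) give a CI of width 0.1 if the AUROC is at least 0.84. The plan used simulation; a closed-form check uses

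var(c) = c(1−c)[1 + (N/2−1)(1−c)/(2−c) + (N/2−1)c/(1+c)] / [N²φ(1−φ)], width = 3.92 × √var(c),

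with N = 337 and φ = 250/337. It gives a width of 0.098 at c = 0.84 and 0.1005 at c = 0.83. The 0.84 is reproduced, and this point does not affect it.

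**2. Age alone, with no assay information.** From the article: 250 symptomatic and 100 healthy controls, that is 250/350 = 71% and 100/350 = 29%. Assumed, because the article gives no age distribution: cases mean 67 (SD 12); symptomatic controls mean 57 to 62 (SD 14 to 15); volunteers mean 45 to 55 (SD 13 to 14). For normally distributed ages,

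AUROC = Φ[(m₁ − m₀)/√(s₁² + s₀²)].

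| Comparison | Smaller gap | Larger gap |
|---|---|---|
| Symptomatic controls | Φ(5/√(12²+15²)) = Φ(0.260) = 0.60 | Φ(10/√(12²+14²)) = Φ(0.542) = 0.71 |
| Volunteers | Φ(12/√(12²+14²)) = Φ(0.651) = 0.74 | Φ(22/√(12²+13²)) = Φ(1.244) = 0.89 |

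The pooled AUROC is the average weighted by control numbers:

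- Smaller gaps: (250 × 0.603 + 100 × 0.742)/350 = 0.64.
- Larger gaps: (250 × 0.706 + 100 × 0.893)/350 = 0.76.

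**3. If symptomatic controls have the same age distribution as cases.** Age gives 0.50 against them, and the pooled figure falls to (250 × 0.50 + 100 × 0.742)/350 = 0.57, or (250 × 0.50 + 100 × 0.893)/350 = 0.61.

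**4. A second set of assumptions.** Take SDs of 11 (cases), 12 (symptomatic) and 14 (volunteers), with gaps of 0 to 10 years against symptomatic controls and 10 to 25 years against volunteers. The pooled age-only AUROC is then 0.56 to 0.79, and against volunteers alone 0.71 to 0.92.

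**5. What age and sex could add to an assay score.** Treat the two as independent normal markers, so that combined AUROC = Φ(√(z_a² + z_g²)), where z_a and z_g are the normal quantiles of the two AUROCs. For an assumed amino acid AUROC of 0.70:

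| Age/sex AUROC | Combined AUROC |
|---|---|
| 0.64 | 0.74 |
| 0.75 | 0.80 |
| 0.80 | 0.84 |

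The last row reaches the plan's benchmark, but it needs an age/sex AUROC above the pooled age-only range in step 2.

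**The case against.** The strongest reply is that the design already contains much of the remedy. Of the controls, 71% are symptomatic patients from secondary care, like the cases, and staff are only a contingency, so the contrast with volunteers is diluted. The use of age and sex is declared openly and allowed for among the 15 parameters in the sample size. The AUROC will be repeated by age band, sex and control type; within a sex stratum sex cannot discriminate, and within an age band age discriminates much less. A separate classifier against symptomatic controls, Shapley values and demographic summaries would all help to show a score driven by age. The article also condenses a fuller protocol, and the SAP is not shown, so further comparisons may exist there.

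Much of this stands, and it limits the point to possible inflation. It does not remove it:

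- The strata describe subgroups and leave the primary AUROC unchanged. With 87 validation controls, four age bands would average 87/4, about 22 controls each.
- Separate classifiers do not remove age or sex differences within each comparison.
- Shapley values apportion predictions; they do not give the AUROC gained over age and sex.
- The article itself states the option to add age and sex and the performance criterion, so the ambiguity does not come from a missing SAP.

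A reader might go further and infer that the AUROC could be high with almost nothing from the assay, so that the study could not answer its question. The documents do not support that. They give no ages, and the pooled age-only figures under either set of assumptions (at most 0.79) stay below 0.84. Nor is it right to call sex an artefact in the tissue-of-origin classifier: that it rules out prostate cancer in women and ovarian cancer in men is true clinical information.

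**Conclusion.** The point holds as a risk of inflation. Age and sex may enter a classifier chosen partly on predictive performance, no matching is described, the validation set shares any cohort differences, and no stated analysis separates the amino acids' contribution. Under assumed gaps of 5 to 10 years (symptomatic controls) and 12 to 22 years (volunteers), age alone would give about 0.64 to 0.76 in the pooled comparison. With symptomatic controls matching the cases in age, that falls to about 0.57 to 0.61. The secondary classifier against healthy volunteers is the most exposed, since age alone could exceed 0.84 there.

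The true size is unknown: it rests on assumed, normally distributed ages, and the effect of sex was not quantified. The sample size figures are unaffected. The plan should be changed, but the point does not undermine the design.

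**What to change.** Prespecify, before the final analysis, that the validation AUROC of the amino-acid-only classifier is reported as the assay's performance. On the same training/validation split:

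1. Fit an age/sex-only benchmark and a combined model.
2. Report the paired difference in validation AUROC (combined minus age/sex-only) with a 95% CI.
3. Report an age- and sex-adjusted AUROC for the amino-acid score, because that score may itself track age.
4. For tissue of origin, report accuracy beside an age/sex-only benchmark, to show what the assay adds while treating sex as legitimate information.

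The planned strata, separate classifiers and Shapley values can stay as supporting analyses. Age and sex are already collected, so no extra recruitment or assay work is needed. The cost is a few lines of analysis text, two further model fits per classifier and a possibly lower headline AUROC.

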### Sample size calculation

A prediction model for a binary outcome (cancer yes/no status, prevalence 74%), 15 prediction parameters (five amino acids Cysteine, Reduced Cysteine, Lysine, Tryptophan and Tyrosine, potentially age and sex, and allowing for additional interactions in models), Nagelkerke’s r-squared of 20% and target shrinkage of 10% requires a minimum sample size of 916 (678 events) to reduce overfitting.^14^ Rounded up to 750 events and allowing a random 3:1 split between data available for model building and validation, the total required sample size is 1000 events, with 250 symptomatic controls, and 100 healthy volunteers, a total of 1350.

Of the 1350, the total sample size for validation would be 337, with 250 cancer cases, 62 symptomatic controls and 25 healthy volunteers. Because the distribution of the linear predictor derived from the prediction model is not known in advance, the anticipated Area Under the Receiver Operator Curve (AUROC) can be used to determine the required sample size for validation.^15^ Using this simulation approach with a target CI width of 0.1, the prediction model’s AUROC must be at least 0.84 to validate the model with sufficient accuracy with 337 individuals. As the pilot data demonstrated an AUROC of 0.98, it seems reasonable to assume an AUROC of 0.84 or higher can be achieved within this study.

### Analysis plan

Baseline medical history, concomitant medications, demographics and Index of Multiple Deprivation will be summarised using descriptive statistics by cohort. The number of symptomatic controls and healthy volunteers who are later diagnosed with cancer and moved into the cancer cases cohort will be presented.

PD will train machine learning algorithms for diagnostic status, ToO and cancer stage. The output for diagnostic status will be a continuous risk score. The output for ToO will be one of the 10 cancers involved in the study, and may include the percentage chance for each ToO. The output for cancer stage will be either stage I, stage II, stage III or stage IV, and may include the percentage chance for each stage. Statisticians at SCTU will produce an AUROC plot in the model training and validation groups for diagnostic status. The apparent c-statistic will be calculated and adjusted for optimism using bootstrapping^16^ with accompanying 95% CIs. Sensitivity will be calculated in each group at cut-offs of 95%, 99% and 99.9% specificity with accompanying 95% CIs. Accuracy of the ToO and cancer stage predictions will be calculated in the model training and validation groups with accompanying 95% CIs.

These analyses will be repeated, stratified by early stage (stage I or II) and late stage (stage III or IV) cancer; ToO; symptomatic controls and healthy volunteers; age band at recruitment; biological sex at birth; availability of screening programme for cancer (screening test available (breast, cervical, colorectal and lung) or not available). All analyses will be conducted in R V.4.4.2 (or higher) or STATA V.17 (or higher).

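### The planned bootstrap optimism adjustment of the training-set c-statistic does not suit several of the listed learners and could leave that figure materially inflated; the held-out AUROC is unaffected

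*Protocol article*

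**What the plan says.** All references are to the protocol article.

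- **Method (Analysis plan).** "The apparent c-statistic will be calculated and adjusted for optimism using bootstrapping", with 95% confidence intervals. AUROC is plotted in both sets: "Statisticians at SCTU will produce an AUROC plot in the model training and validation groups for diagnostic status". The analyses are then repeated by stage group, tissue of origin, control type, age band, sex and availability of screening.
- **Who does what.** "PD will train machine learning algorithms for diagnostic status, ToO and cancer stage" (Analysis plan). For cancer status, "The output for diagnostic status will be a continuous risk score". What passes to the trials unit is described in Machine learning training and validation: "These predictions will be provided to statisticians at SCTU to independently validate predictions against true status".
- **Learners (same section).** The candidates are "random forests, support vector machines, ensemble subspace discriminant classifiers, XGBoost, neural networks and deep learning algorithms". None is chosen yet: "The final modelling strategy will be informed by comparative predictive performance and computational cost". Cross-validation appears once: "Stratified cross-validation will be used to reduce overfitting".
- **Held-out set.** Model training and validation assigns 25% of participants to a validation set, with PD blinded to their diagnoses. Sample size calculation plans that set at 337 people (250 cases, 87 controls) and aims for a confidence interval of width 0.1 on the AUROC.

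**The concern.** Optimism in a c-statistic comes from fitting: choosing an algorithm, tuning it and estimating it on the same people on whom it is scored. A bootstrap can measure optimism only if those steps are rerun in each resample. The article describes a flow of finished predictions from PD to SCTU and mentions no rerun. Resampling finished scores shows how variable the apparent AUROC is, but not how optimistic it is.

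A second difficulty arises even if PD does rerun the fit. The ordinary optimism bootstrap tests each refitted model on the original sample, most of which that model has already seen. A smooth, low-capacity model loses little by this. A learner that nearly memorises its training data still looks excellent on the original sample, so the estimated optimism is too small.

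At stake is a published training-set AUROC that is labelled as adjusted for optimism but may still carry most of it. Readers may trust the label, particularly in the subgroup repeats. There the validation set is thin: 250 cases over 10 cancers is about 25 each if evenly spread.

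**Working it through.** **The plan's own figures.** The article gives no figure for the adjusted c-statistic. Its related sample-size figures reproduce and are not in dispute.

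- Development: n = P / [(S − 1) ln(1 − R²/S)], with P = 15, S = 0.9 and R² = 0.20 × 0.682 ≈ 0.136 (0.682 is the maximum Cox–Snell R² at prevalence 0.74). This gives 15 / [−0.1 × ln(1 − 0.136/0.9)] = 915.6, so 916, and 916 × 0.74 = 678 events.
- Validation: with n = 337, prevalence 0.74 and Newcombe's standard error, the interval width is 0.1003 at AUROC 0.83 and 0.0975 at 0.84. This matches the stated threshold of 0.84.

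**The correction.** For bootstrap sample b with refitted model M_b:

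optimism = mean over b of [AUC(M_b in sample b) − AUC(M_b in original sample)]; corrected = apparent − optimism.

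**Step 1: fixed scores.** If M_b is the same score vector every time, the bracket averages to about zero. In simulation the mean was 0.0000 to 0.0003 for each of the four learner settings run. A random forest with apparent AUROC 1.00 stayed at 1.00, against 0.68 or 0.80 in new subjects.

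**Step 2: full refit, reason for the shortfall.** A bootstrap sample contains about 63.2% of the original subjects. The share of case–control pairs in the original sample with at least one member already seen is 1 − 0.368² ≈ 0.86.

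**Step 3: full refit, size.** From the article: 75% of 1000 cases = 750, and 75% of 350 controls ≈ 262. There are seven inputs (five amino acids, age, sex). Assumed: Gaussian predictors, best achievable AUROC 0.74 or 0.84, and mostly default tuning. Each new-subject AUROC comes from 10,100 simulated people. Rows marked * use 8 replicates × 20 bootstraps; the others use 3 × 10. Entries are apparent → corrected (new subjects), then the inflation that remains.

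| Learner | Best AUROC 0.74 | Remains | Best AUROC 0.84 | Remains |
|---|---|---|---|---|
| Random forest* | 1.000 → 0.943 (0.681) | 0.26 | 1.000 → 0.960 (0.795) | 0.16 |
| Random forest, library default | 1.000 → 0.947 (0.695) | 0.25 | 1.000 → 0.964 (0.806) | 0.16 |
| Random forest, minimum leaf 20* | 0.900 → 0.795 (0.705) | 0.09 | 0.925 → 0.859 (0.808) | 0.05 |
| Boosting, depth 6 | 1.000 → 0.923 (0.678) | 0.25 | 1.000 → 0.951 (0.793) | 0.16 |
| Boosting, depth 3 | 0.954 → 0.848 (0.697) | 0.15 | 0.975 → 0.907 (0.809) | 0.10 |
| RBF kernel, light penalty, untuned* | 0.950 → 0.818 (0.645) | 0.17 | 0.966 → 0.873 (0.762) | 0.11 |
| RBF SVM, default | 0.832 → 0.739 (0.673) | 0.07 | 0.879 → 0.825 (0.798) | 0.03 |
| Small neural network | 0.791 → 0.722 (0.719) | 0.00 | 0.872 → 0.831 (0.827) | 0.00 |
| Subspace discriminant* | 0.734 → 0.725 (0.731) | −0.01 | 0.832 → 0.828 (0.833) | −0.01 |

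For the first row at 0.74, the true optimism is 1.000 − 0.681 = 0.319 and the estimated optimism is 1.000 − 0.943 = 0.057, so about 18% is removed. A separate run gave 0.945 against 0.685, and 0.964 against 0.815.

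**Step 4: does a replacement do better?** Ten-fold cross-validation with refitting in each fold, against new subjects:

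- Random forest: 0.683 vs 0.681, and 0.790 vs 0.795.
- RBF kernel: 0.634 vs 0.645, and 0.751 vs 0.762.
- Subspace discriminant: 0.723 vs 0.731, and 0.826 vs 0.833.

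None shows a material upward bias. Cross-validation was not run for boosting, the SVM or the neural network.

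**The case against.** The case for leaving the plan alone has real force.

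- **The article is condensed.** It says that predictions go to SCTU, but not that nothing else does, and the bootstrap sentence does not say who refits. A reader might infer that the correction cannot work at all. The text does not support that, because refitting by PD or transfer of the pipeline is not excluded. This limits Step 1 but leaves Step 3 untouched.
- **The bootstrap variant is not named.** A .632+ bootstrap would also fit the wording. For an untuned RBF kernel classifier it gave 0.504 against 0.500 on pure noise, and 0.828 against 0.810 at best AUROC 0.84. Bootstrapping as such is therefore not the fault; the ordinary optimism version is.
- **Tuning matters.** With the kernel classifier tuned by cross-validation, the ordinary refit bootstrap was accurate when there was signal (0.623 vs 0.625, 0.746 vs 0.745, 0.835 vs 0.840) and biased only on noise (0.576 vs 0.496). The pilot's own classifier type, the subspace discriminant, is hardly affected. A reader might infer that the training AUROC will be inflated whatever is chosen; that depends on a learner not yet selected.
- **The held-out estimate stands.** A reader might infer that the validation AUROC is also to be corrected, or that the adjusted training figure replaces it. Neither follows. An apparent c-statistic is by definition a training-data figure, and the article sizes, blinds and reports the validation set separately.

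What survives is that the plan fixes a correction while keeping open learners for which its ordinary form fails badly.

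**Conclusion.** The point holds for the training-set c-statistic and its subgroup repeats, at moderate severity. On fixed scores the adjustment removes essentially nothing. With full refitting and the ordinary optimism bootstrap, the inflation left is about 0.16 to 0.26 for random forests at usual settings and for deep boosting, and 0.10 to 0.15 for shallow boosting. It is 0.03 to 0.07 for a default RBF SVM (0.11 to 0.17 for a lightly penalised kernel classifier), and about zero for a small neural network and a subspace discriminant.

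These sizes are illustrative. They rest on assumed Gaussian predictors, two assumed levels of achievable AUROC, mostly default tuning and few replicates. A large leaf size cut the random forest's residual to 0.05 to 0.09. The direction has a structural cause and does not hang on those choices alone. The validation AUROC and the sample-size figures are not called into question.

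**What to change.** 1. Name the unadjusted AUROC in the 25% validation set as the primary estimate, with a DeLong or participant-level bootstrap confidence interval.
2. For the training set, replace the ordinary optimism correction in one of two ways:
   - PD sends SCTU out-of-fold scores from repeated, nested cross-validation that repeats tuning and algorithm selection within each fold, and SCTU computes the AUROC from them. This builds on the stratified cross-validation already planned.
   - A .632+ or out-of-bag bootstrap is used, with the whole pipeline refitted in every resample, and the plan states who runs it.
3. Apply the same choice to the training-set subgroup repeats.

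The cost is a change of wording and some computing time at PD. The training AUROC will look less favourable. The change should be made before the final models are trained.
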